### Patient termination and withdrawal criteria

Participants and their authorised surrogates will participate in the study voluntarily, and therefore they may withdraw from the trial at any time for any reason. Patients may also be withdrawn from the study for: (1) severe adverse events; or (2) violating or deviating from the protocol. If a patient is withdrawn for one of the two reasons mentioned, they should proceed to security analysis.

### Research centre termination and withdrawal criteria

A research centre must terminate their involvement in the clinical trial if: (1) the researchers do not obey the rules of the International Conference on Harmonisation Guidelines for Good Clinical Practice or local regulations; (2) the research centre intentionally submits incorrect or incomplete data to inspectors; (3) the requirements of the protocol are not met, including poor data quality (incomplete case report forms); or (4) investigators make changes without informing the lead researchers. Each investigator should be qualified and be approved by the lead researchers. As a 10% dropout rate is allowed, there will be no need to add new patients when an existing participant withdraws from the trial.

### Data collection and inspection

The principal investigators will centralise all of the data monthly and send a newsletter to each centre to promote data quality and the process of the trial. Data collection begins on the day a participant signs the informed consent and continues until the participant is discharged or transferred to another hospital. Data are collected using a paper based case report form (see online supplementary file–data collection form) and an electronic database.

Investigators follow a schedule to collect data, including: (1) screening data, informed consent, demographic data, inclusion and exclusion criteria, and enrolment data; (2) baseline information on catheterisation (age, gender, ID, height, weight, risk factor for infection, Sequential Organ Failure Assessment (SOFA) score, Acute Physiology and Chronic Health Evaluation II (APACHE II) score, underlying diseases and antibiotic therapy), vascular ultrasound of veins at the insertion site and contralateral site, and CVC catheterisation (date, temperature, catheter type, insertion site, neutrophil count, antibiotic therapy, other type of catheterisation and serious adverse effects); (3) CVC removal data (duration of catheterisation, temperature, reason for catheter removal, parenteral nutrition and neutrophil count), peripheral blood cultures, catheter blood cultures, catheter tip cultures and vascular ultrasound of veins at the insertion site and contralateral site; and (4) prognosis, date of transferring out of the intensive care unit and date of discharge/death, whichever comes first.

### Follow-up data

Statistical analysis plan

#### Hypothesis

The study hypothesis is:

$$H_{0}:\Pi CVCp=\Pi CVC$$

$$H_{1}:\Pi CVCp<\Pi CVC$$

Where Π represents the incidence of CRBSI.

#### Analysis sets

There will be a full analysis set, a per protocol set and a safety set (see online supplementary appendix–supplemental method).

### Statistical analysis

#### Principles

All statistical tests will be two tailed and will be analysed using SAS statistical analysis software (V.9.4; SAS Institute, Cary, North Carolina, USA). Quantitative variables will be analysed by calculating the mean, SD, median, minimum value, maximum value, lower quartile (Q1) and upper quartile (Q3). Categorical variables will be described using cases and percentages for each category. The significance of differences between two groups will be determined using the χ^2^ test or Fisher’s exact test for categorical data, the group *t* test or Wilcoxon rank sum test for continuous data and the Wilcoxon rank sum test or the Cochran–Mantel–Haenszel χ^2^ test for ranked data.

#### Proposed primary analysis

The incidence of CRBSI in the two groups will be compared using the Cochran–Mantel–Haenszel χ^2^ test and stratified analysis based on the time CRBSI occurs. For the interim analysis, the size of the test for α_1_ is 0.003, and we will also calculate (1−α_1_)×100% CI. If the result rejects H_0_, then the antimicrobial CVC group is superior to the ordinary CVC group. If the interim analysis shows no statistical significance or if the data safety monitoring board decides to complete the next stage of the trial, we will complete the final analysis (α_2_=0.049, CI (1−α_2_)×100%). The proposed primary analysis is based on the final analysis set and the per protocol set. Table 2 shows the alpha spending functions and cut-off values.

**Table 2 T2:** Alpha spending functions and cut-off values

	Lower bound	Upper bound	Alpha size of test	Alpha spending	Cumulative alpha	Power of test	Overall efficiency
Interim analysis	−2.96259	2.96259	0.003051	0.003051	0.003051	0.164276	0.164276
Final analysis	−1.96857	1.96857	0.049002	0.046949	0.050000	0.636018	0.800294

The distribution of suspension boundary (alpha) is normal distribution.

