**Methods and analysis:**

In this multicentre trial, we will randomly assigned dual lumen central venous catheterisation (≥5 ds) in patients in the adult ICU to the antimicrobial central venous catheter (CVC) group or the ordinary CVC group. We plan to recruit 12–16 medical centres in China. Our main objective is to assess the effectiveness of antimicrobial CVCs in reducing catheter related bloodstream infection (CRBSI), all cause mortality, catheter colonisation, catheter related thrombosis and other catheter related complications. The primary outcome is the incidence of CRBSI.

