### Study population

The study sample size is calculated on the basis of an expected CRBSI rate of approximately 6% for the control group and 3% for the antiseptic catheter group. Allowing for a 10% dropout rate, 1818 patients are required to yield a study with 80% power at a statistical significance level of 0.05.

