### Randomisation

Each research centre will receive sequentially numbered containers used to implement the random allocation sequence, and the treatment allocation group will be hidden beyond the coated card. To ensure that patients are randomly assigned at a 1:1 ratio at each study centre, the randomised cards will be protected using a block design (each block includes four random allocation sequences). For a patient who meets the required criteria, the local investigator opens a randomised card that records the screening number and treatment allocation group. Then, the physician in charge of the patient will obtain the correct study catheter and complete catheterisation. Hence treatment allocation will be concealed.

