#### Secondary analysis

The incidence of catheter tip colonisation, CRT and hospital mortality in the two groups will be compared using the χ^2^ test or Fisher’s exact test, or random intercept logistic regression. Analyses of the other indicators follows the process described under ‘Principles’ above. Analyses of the secondary indicators is based on the full analysis set and the per protocol set.

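### The only stratifier named for the primary CMH test, the time CRBSI occurs, is part of the outcome: taken literally the statistic is 0/0, and the readings that can be computed are not stated

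*Protocol article*

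**What the plan says.** Under Proposed primary analysis, the protocol article states that CRBSI in the two groups will be "compared using the Cochran–Mantel–Haenszel χ^2^ test and stratified analysis based on the time CRBSI occurs". The only stratifier it names is in the closing words, "stratified analysis based on the time CRBSI occurs". The interim and final significance levels (0.003 and 0.049, detailed in Table 2) are attached to this comparison.

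Elsewhere the article treats the endpoint as a simple proportion. The abstract says "The primary outcome is the incidence of CRBSI". Under Hypothesis, the tested parameter "represents the incidence of CRBSI". Under Study population, the sample size assumes an "expected CRBSI rate of approximately 6% for the control group and 3% for the antiseptic catheter group", with "80% power at a statistical significance level of 0.05", 10% dropout and 1818 patients.

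Under Randomisation, cards are prepared in blocks of four: "To ensure that patients are randomly assigned at a 1:1 ratio at each study centre". The primary analysis text does not mention centre. It also gives no time intervals, no risk sets and no rule for putting a patient without CRBSI into a time stratum.

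**The concern.** A CMH test on a binary outcome compares the arms within strata that each contain patients with and without the event. Strata are normally baseline factors, so that belonging to one does not depend on treatment or outcome. The time of CRBSI is a feature of the outcome itself, and a patient who never has CRBSI has no value for it.

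This is the trial's confirmatory test, and it also drives a possible early stop for efficacy. If the written rule cannot be computed, whoever runs the analysis must choose a substitute, possibly after seeing data by arm. The primary p value would then rest on a choice that the plan did not make.

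**Working it through.** **Inputs.** From Study population: 6% and 3%, 80% power, alpha 0.05, 10% dropout, N = 1818. From Principles: two-sided tests. From Table 2: bounds 2.96259 and 1.96857, nominal alphas 0.003051 and 0.049002. From Randomisation: 1:1 allocation.

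**1. The plan's own figures.** Pooled two-proportion formula, per arm, with mean proportion 0.045:

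n = [z(α/2)·√(2 × 0.045 × 0.955) + z(power)·√(0.06 × 0.94 + 0.03 × 0.97)]² / 0.03²

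- α = 0.05: (1.960 × 0.2932 + 0.8416 × 0.2924)² / 0.0009 gives 749 per arm. With the continuity correction, 814 per arm, 1628 in total, and 1628 / 0.9 = 1809.
- α = 0.049002: 753 per arm. With the correction, 819 per arm, 1638 in total, and 1638 / 0.9 = 1820.

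These bracket 1818. Without the correction α = 0.05 gives 1665, and one-sided variants give 1312 to 1467, so those do not reproduce it. The sample size therefore rests on an unstratified comparison of two proportions. Table 2 also reproduces: with one look at half the information, the two bounds give a cumulative alpha of 0.0500.

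**2. Who has an event time.** 1818 × 0.9 ≈ 1636 evaluable, 818 per arm. Expected cases: 818 × 0.06 ≈ 49 and 818 × 0.03 ≈ 25, or 74 in total. That is about 4.5%, and the other 95.5% have no event time.

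**3. The literal reading.** In a stratum of N patients (n1 antimicrobial, n0 control) with m cases, a of them in the antimicrobial arm:

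a − E = a − n1·m/N, and variance = n1·n0·m·(N − m) / [N²(N − 1)]

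- A time stratum holds only cases, so m = N and a = n1. Then a − E = 0, and the factor (N − m) makes the variance 0.
- A stratum of non-cases has m = 0, so both terms are again 0.

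Example: split the 25 and 49 cases over three bands as 10/20, 9/17 and 6/12 (an assumed split; any other gives the same result). In the first band E = 10 × 30/30 = 10, so a − E = 0, with variance 0. Summed over all strata, the statistic is 0/0. Dropping the non-cases does not help, because the remaining strata hold only cases.

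**4. The same data without event-time strata.** a − E = 25 − 818 × 74/1636 = −12. Variance = 818 × 818 × 74 × 1562 / (1636² × 1635) = 17.67. Chi-square = 144 / 17.67 = 8.15 on 1 df.

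**5. Risk sets over the same three bands.** Patients still at risk are 818/818, then 808/798, then 799/781. The sum of a − E is −12.18 and the variance 18.22, so chi-square = 8.15. If 250 and then 300 patients per arm are assumed to leave after the first two bands, it is 8.59.

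**6. Simulation of the readings.** 3000 trials, 818 per arm, tested at 0.05. Assumed, because the article gives no such figures: catheter removal at 3 days plus an exponential time with mean 7 days, unrelated to arm or infection; a constant CRBSI hazard; bands cut at days 5, 8 and 12.

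| Reading | Type I error | Power |
|---|---|---|
| Literal event-time strata | undefined in every trial | undefined in every trial |
| No time strata | 4.9% | 83% |
| Risk sets over time bands | 4.8% | 84% |
| Non-cases placed by removal time | 5.2% | 82% |

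The Monte Carlo standard error of a 5% rate is √(0.05 × 0.95/3000) ≈ 0.4 points, so the three type I errors cannot be told apart from 5%. The literal row follows from step 3 and needs no simulation.

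**7. Power of the simple test.** With 818 per arm at 0.049002: Φ[(0.03 × √818 − 1.96857 × 0.2932) / 0.2924] = Φ(0.961) = 0.83.

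**The case against.** The strongest reply is that the sentence can be read as naming two things: a CMH test of incidence, and a separate breakdown by time. Principles gives some support, since it lists the CMH test for ranked data without naming strata. A second reply is that a Mantel–Haenszel test over time intervals, using patients still at risk in each, is an established log-rank type analysis. Steps 5 and 6 show that it can be computed and holds its size. A third is that a journal article leaves the choice of adjustment factors to the SAP.

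The first two replies stand as possible intentions, but neither is stated. The risk-set version also needs intervals and a rule for leaving the risk set, and it compares hazards, whereas Hypothesis and the sample size concern incidence. If timing is a separate analysis, the CMH test has no stated stratifier and the sentence still has to be separated into two. The third reply would meet a complaint of missing detail. Here a stratifier is named, and in its literal sense it does not work; a fuller document would have to depart from the sentence, not merely add to it.

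A reader might infer that the primary result would be biased. The documents do not support that. Placing non-cases by removal time conditions on something observed after randomisation, which could mislead if removal depends on arm or on suspected infection. Under non-informative removal, however, the type I error was 5.2%, which is not material inflation.

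**Conclusion.** The point holds in this form: the only stratifier named for the primary comparison is undefined for about 95.5% of patients at the planned rates, and used literally it makes the CMH statistic 0/0. That result is algebraic and rests on no assumption about rates or timing. The planned rates enter only the 95.5% and the worked examples.

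The readings that can be computed gave similar answers in the illustration (chi-square 8.15 to 8.59) and similar power (82% to 84%), under the assumed removal pattern. What is at stake is therefore not a demonstrated loss of power or validity, but a confirmatory test, with an efficacy look, that the text does not fix.

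Three further inferences are not supported:

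- That the sample size is wrong: 1818 rests on an unstratified comparison and is unaffected.
- That the trial ignores centre: the SAP is not shown, and no effect of leaving centre out has been calculated. Centre matters here as the obvious baseline factor to put in place of event time.
- That the methods under Secondary analysis must change, including the option "or random intercept logistic regression": nothing in this point bears on them.

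The 83% power applies to the unstratified test at a single look at the final level. Power of the centre-stratified test was not computed.

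**What to change.** Replace the sentence under Proposed primary analysis with wording such as: CRBSI incidence will be compared between groups by the CMH chi-square test stratified by study centre; the common risk difference will be reported with a confidence interval at the interim and final alpha levels (99.7% and 95.1%, from 1 − 0.003 and 1 − 0.049).

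Add a rule, set before unblinding and so before the interim analysis, for pooling very small centres. With about 74 cases over 12 to 16 centres, the average is only 74/16 ≈ 4.6 to 74/12 ≈ 6.2 cases per centre, and roughly half that at a look halfway. A centre with no cases adds nothing to the statistic.

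If the timing of CRBSI is of interest, describe it as a separate, non-primary analysis using risk sets or cumulative incidence, with its time origin, end of follow-up and handling of death stated.

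The cost is a few sentences of wording. Centre is already known for every patient through the randomisation, no new data are needed, and 1818 and the Table 2 boundaries stay as they are.

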#### Secondary analysis

The incidence of catheter tip colonisation, CRT and hospital mortality in the two groups will be compared using the χ^2^ test or Fisher’s exact test, or random intercept logistic regression. Analyses of the other indicators follows the process described under ‘Principles’ above. Analyses of the secondary indicators is based on the full analysis set and the per protocol set.

#### Subgroup analysis

Subgroup analyses will be conducted for predefined factors, such as insertion site, catheter duration, antibiotic therapy, anticoagulation therapy, underlying diseases, body mass index, SOFA score, APACHE2 score, etc. Other exploratory subgroup analyses will be conducted eventually.

#### Safety analysis

The proportion of abnormal cases after treatment will be determined, as will the number of cases/incidence of adverse events and severe adverse events. We will also describe the clinical manifestations, degree of all adverse events, and the relationship between these factors and the catheters in detail. Changes in indexes will be described using a crosstab grid. All safety evaluations will be based on the safety set.

#### Missing data

Worst observation carried forward will be used to evaluate missing data in the full analysis set. Dropout rates will be obtained, and for each group we will determine if the dropout rate is higher than the difference in event rates between the two groups using the worst case scenario model.

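### Worst observation carried forward has no clear meaning for CRBSI: depending on how it is read, full-analysis-set power at the planned 10% dropout is about 38% or about 83%, and the accompanying worst-case check can reassure only if dropout stays below about 3%

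*Protocol article*

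**What the plan says.** The Missing data section of the protocol article gives two rules. The first is: "Worst observation carried forward will be used to evaluate missing data in the full analysis set". The second is a check in which the trial will obtain dropout rates and, for each group, "determine if the dropout rate is higher than the difference in event rates between the two groups using the worst case scenario model". No consequence is attached to either answer.

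The Study endpoints section defines CRBSI from catheter-tip colonisation together with blood-culture results. The Data collection and inspection section lists the tip, catheter-blood and peripheral-blood cultures with the CVC removal data, and Table 1 schedules cultures only after allocation.

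The Study population section plans on "an expected CRBSI rate of approximately 6% for the control group and 3% for the antiseptic catheter group" and says: "Allowing for a 10% dropout rate, 1818 patients are required", for "80% power at a statistical significance level of 0.05". The section on research centre termination adds that, because 10% dropout is allowed, withdrawn patients are not replaced. The article leaves the definitions of the analysis sets to a supplementary appendix, which is not at hand.

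**The concern.** Carrying forward the worst observation is a rule for outcomes measured repeatedly. For a culture-based outcome settled around catheter removal, a patient who leaves without the cultures normally has nothing to carry. Two readings remain:

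- **Reading A:** the worst possible value, so the patient is counted as CRBSI.
- **Reading B:** the worst value seen so far, so the patient is counted as no CRBSI.

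They act in opposite directions on both event rates, and the article does not say which applies. The choice could therefore be made after data are seen.

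Under reading A, many imputed events are added equally to both arms and dilute the difference. Under reading B, both rates are understated if any of the missing patients would have had CRBSI. Under either, a single imputed value enters the test as if it had been observed.

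The second rule compares a quantity planned at 10% with one planned at 3 points. At those values its answer is known in advance.

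**Working it through.** **Inputs.** CRBSI 6% v 3%, N = 1818 and 10% dropout (Study population); 1:1 allocation (Randomisation), so 909 per arm; two-sided tests (Principles); final-analysis boundary 1.96857, alpha 0.049 (Proposed primary analysis and Table 2). Missing patients are assumed to have the same underlying CRBSI rates as the others, with missingness equal in both arms.

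**The plan's own figure.** The two-sided two-proportion formula with continuity correction gives 814 per arm at alpha 0.05: 1628/0.9 = 1809. At alpha 0.049 it gives 819 per arm: 1638/0.9 = 1820. The stated 1818 lies between (818 × 2/0.9 = 1818). So the calculation takes dropouts out of the denominator and leaves about 818 evaluable per arm. Power at 818 per arm is 80% with continuity correction and 83% without.

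**Power formula** (uncorrected, n per arm, p̄ the mean of the two rates):

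power = Φ{ [ |p1 − p2|·√n − 1.96857·√(2p̄(1 − p̄)) ] / √(p1(1 − p1) + p2(1 − p2)) }

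**Reading A, missing counted as CRBSI:** p = d + (1 − d)·p0.

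- At d = 0.10, control is 0.10 + 0.9 × 0.06 = 15.4% and antimicrobial is 0.10 + 0.9 × 0.03 = 12.7%, a difference of 2.7 points.
- With n = 909: (0.814 − 0.967)/0.491 = −0.312, so power is 37.7%.
- Cross-checks: 38.0% with both group-sequential looks, 37.7% by simulation, 35.2% with continuity correction.
- About 5,230 patients in total would be needed for 80% power (5,378 with continuity correction).

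**Reading B, missing counted as event-free:** p = (1 − d)·p0.

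- At d = 0.10, the rates are 5.4% v 2.7%, again a difference of 2.7 points.
- (0.814 − 0.549)/0.278 = 0.954, so power is 83.0%.
- With continuity correction, replace n by (909 − 1/0.027)²/909 = 836; power is about 80%.

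| Missing CRBSI status | Rates, reading A | Power, reading A |
|---|---|---|
| 2% | 7.9% v 4.9% | 72% |
| 5% | 10.7% v 7.85% | 55% |
| 10% | 15.4% v 12.7% | 38% |

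**Imputed against real events, reading A at 10%** (percentage points of each arm): control 10/5.4 = 1.9; antimicrobial 10/2.7 = 3.7; overall 20/8.1 = 2.5.

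**The worst-case check.** Planned dropout over planned difference is 10/3, or more than threefold. In the extreme case (antimicrobial-arm missing all events, control-arm missing all non-events) at 10%, the rates are 5.4% control v 12.7% antimicrobial, a reversal of 7.3 points. The difference vanishes where (1 − d) × 0.06 = d + (1 − d) × 0.03, that is d = 0.03/1.03 = 2.9%.

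**The case against.** The strongest reply is that the 38% is one branch only, and an upper-end one.

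- **Literal reading.** Carrying forward an observed value makes a patient with no CRBSI seen a non-event. That reading costs essentially no power: 83%, the same as the uncorrected figure for 818 evaluable per arm. A reader might infer that the rule as written cuts power to 38%, or that the stated 80% must be wrong. The text does not support either. The 80% fails to describe the analysis under reading A only.
- **Unseen definitions.** The full analysis set is defined in an appendix not shown, so whether every dropout enters it is unknown. In addition, the primary analysis section names a final analysis set, which is taken here to mean the full analysis set.
- **Dropout is not missing CRBSI.** Patients withdrawn for a severe adverse event or a protocol deviation may still have removal cultures. The 10% is a planning allowance.
- **Timing.** The CRBSI definition includes a differential time-to-positivity route, and the primary analysis stratifies by time of CRBSI, so some cases may be recorded before removal. But a patient already recorded as CRBSI is not missing. For the rest, any earlier status would be negative, which is reading B.
- **The check uses observed dropout.** A reader might infer that it must always fail. It need not: it is close to a shortcut for the extreme worst case and would inform if dropout were below about 3%. No pass or fail is attached to it.
- **Per protocol set.** The primary analysis also uses this set. The carry-forward rule is stated for the full analysis set only. This does not rescue the randomised comparison, because the per protocol set is a selected group.

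All of these stand as limits on the size of the problem. None tells the analyst how to code a missing CRBSI. The objection is to a method that the article itself states, so it does not depend on detail left to an analysis plan.

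**Conclusion.** The carry-forward rule is badly fixed for the primary endpoint. If all of the planned 10% lack CRBSI status and remain in the full analysis set, power is about 38% or about 83% according to an unstated reading. The gap narrows as missingness falls: at 2% missing, reading A still gives 72%. These are unstratified normal-approximation figures for the planned rates. They set aside the Cochran–Mantel–Haenszel stratification and assume equal missingness by arm. On the continuity-corrected basis that reproduces 1818, the pair is about 35% and 80%.

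The worst-case check is exceeded more than threefold at the planning values. At the planned effect it can reassure only if dropout is below about 3%, and the article says nothing about what follows when it is exceeded.

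Severity: should-fix. The point bears on the primary result, but the size of the loss depends on the reading, on the unseen set definition and on how many dropouts truly lack the endpoint.

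**What to change.** 1. Remove worst observation carried forward for CRBSI. Analyse all observed data in the full analysis set, with multiple imputation of missing CRBSI status by arm from variables already collected: centre, APACHE II and SOFA scores, catheter days, and any available culture results.
2. Replace the dropout-versus-difference comparison with a tipping-point analysis over arm-specific CRBSI rates among those with missing status. Keep the extreme worst case as its end point, so what the present check was meant to show is retained.

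The cost is a change of wording and modest extra programming. No new data are needed.
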